### Outcomes {12}

Table 3 presents an overview of the time points for each outcome measurement.

**Table 3 Tab3:** Measures

	*Measures*				Measurement			
	Measure	Items	Respondent*	Type	T(0)	T(1–11)	T(12/14)	T(13)
Child PTSD	CAPS-CA		c	Interview	*			*
	CRIES	13	cp	Questionnaire	*	*	*	*
	TSCC	54	c	Questionnaire	*		*	*
Child functioning	SDQ	25	cp	Questionnaire	*		*	*
	CDI	28	c	Questionnaire	*		*	*
	CDC	20	p	Questionnaire	*		*	*
Parent functioning	NOSI-K	25	p	Questionnaire	*	*	*	*
	Trauma-informed	6	p	Questionnaire	*		*	*
	IES-r	22	p	Questionnaire	*		*	*
	YAS-R	29	p	Questionnaire	*		*	*
	DPAS	9	p	Questionnaire	*		*	*
Structural emotional and physical safety	CTS	77	p	Questionnaire	*		*	*
	CTS-pc	27+39	c	Questionnaire	*		*	*
	PRTI	21	p	Questionnaire	*		*	*
	ACE-Q	10	p	Questionnaire	*		*	*
	New IPV incidents	8	cp	Questionnaire	*	*	*	*
	SIS	43	c	Questionnaire	*		*	*
	SIFS	7	c	Questionnaire	*		*	*
	SIM-PR	28	p	Questionnaire	*		*	*
	Security scales	15	cp	Questionnaire	*		*	*
	FIT	4 tasks	cp	Observation			*	
Total items child					232	21	232	232
Total items parent					335	46	335	335

Marked measures are part of routine outcome measuring

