#### Primary outcomes

##### Child PTSD symptoms

The Clinician-Administered-Ptsd-Scale-Children-And-Adolescents (CAPS-CA) [55] is a standardized clinical interview, to assess PTSD conform the DSM-5 standards. A Dutch translation of the CAPS-CA [56] is administered to children aged 8–18. The core traumatic event is chosen based on the life events checklist. If the core traumatic event is a sequence of events, which is often the case in family violence, a brief term is chosen to capture the core of these events. The CAPS-CA assesses the frequency and intensity in which each PTS disorder symptoms occur. A 5-point severity rating scale is used for all symptoms, ranging from 0 (= absent) to 4 (= extreme/incapacitating). An example item is *In the past month, have you had upsetting thoughts, pictures or sounds of what happened come into your mind when you didn’t want them to?*. A total symptom severity score is calculated by summing the severity scores for items 1–20. A total symptom score can also be calculated per cluster; re-experiencing (items 1–5), avoidance (items 6 and 7), negative alterations in cognitions and mood (items 8–17), and hyperarousal (items 15–20). A symptom cluster score may also be calculated for dissociation by summing items 29 and 30. To determine the PTSD diagnostic status, individual symptoms should be dichotomized as “present” or “absent”. A symptom is considered present only if the corresponding item severity score is rated 2 (= moderate/threshold or higher). Items 9 and 11–20 have the additional requirement of a trauma-relatedness rating of definite or probable. The DSM-5 diagnostic rule requires the presence of at least one criterion B symptom, one criterion C symptom, two criterion D symptoms, and two criterion E symptoms. Also, criteria F (disturbance at least 1 month) and G (disturbance that causes either clinically significant distress or functional impairment) must be met. Reliability of the CAPS-CA in a Dutch sample for the total scale ranged from coefficient *a* of 0.77 to .86, and the interrater reliability of the total scale is 0.99. Caps-CA also demonstrated divergent, convergent, and discriminant validity [57].

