##### Emotional security and physical safety

To assess the severity and intensity of the violence that children have been exposed to, a combined measure will be used including items from the Conflict Tactics Scale (78 items, 8-point rating scale) [64], the Conflict Tactics Scale parent child (27 and 39 items, 8-point rating scale) [64], the Parents Report of Traumatic Impact (21 items ) [65], and the Adverse Childhood Experience Questionnaire (10 items, 5-point rating scale) [66]. An example item is *I punched or hit my partner with something that could hurt*. This combined questionnaire has been used in a previous study on the effectiveness of a psycho-educational prevention program for children exposed to IPV [67]. The questionnaire covers the topics and duration of the violence and the nature of the arguments in the relationship with the (ex-partner), followed by items from the Conflict Tactics Scale parent child and Parents Report of Traumatic Impact about problems between parent and child, and traumatic events the child has experienced. The questionnaire also includes items about traumatic experiences in parents’ own childhood. A short questionnaire of 8 items for parent and child is added to assess if any new IPV incidents or other stressful events occurred.

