## Statistical methods

### Statistical methods for primary and secondary outcomes {20a}

The measurement level of each variable is at least ordinal. We control for the duration and severity of family violence [96], child functioning, parental psychopathology [97], and new incidents of family violence as a priori potential confounders. Analyses will be performed using the latest version of the software package Statistical Package for the Social Sciences (SPSS). First, to determine whether changes on continuous measures are different per treatment, we use linear mixed models. Continuous measures with only one time point will be analysed with independent samples *T*-test. Changes in categorical outcomes over the course of treatment across the conditions are tested with generalized estimating equations (GEE). To handle missing data, we will use maximum likelihood estimation within the linear mixed model analyses. For the planned GEE, we will explore the possibilities to deal with missing data, depending on the amount, randomness, and type of data missing. Analyses will primarily be performed according to the principles of intention-to-treat; however, they will be repeated as per-protocol analyses (see Table 4).

**Table 4 Tab4:** Statistical analyses

*Statistical analyses*					
	Measure	Type of data	Timepoints	Statistical analysis	Subjects
Child PTSD	CAPS-CA	Categorical	3	GEE	ITT/PP
	CRIES	Continuous	4	Mixed models	ITT/PP
	TSCC	Continuous	3	Mixed models	ITT/PP
Child functioning	SDQ	Continuous	3	Mixed models	ITT/PP
	CDI	Continuous	3	Mixed models	ITT/PP
	CDC	Continuous	3	Mixed models	ITT/PP
Parent functioning	NOSI-K	Continuous	4	Mixed models	ITT/PP
	Trauma-informed	Continuous	3	Mixed models	ITT/PP
	TSI	Continuous	3	Mixed models	ITT/PP
	YAS-R	Continuous	3	Mixed models	ITT/PP
	DPAS	Continuous	3	Mixed models	ITT/PP
Structural emotional and physical safety	CTS	Continuous	3	Mixed models	ITT/PP
	CTS-pc	Continuous	3	Mixed models	ITT/PP
	PRTI	Continuous	3	Mixed models	ITT/PP
	ACE-Q	Continuous	3	Mixed models	ITT/PP
	New IPV incidents	Continuous	4	Mixed models	ITT/PP
	SIS	Continuous	3	Mixed models	ITT/PP
	SIFS	Continuous	3	Mixed models	ITT/PP
	SIM-PR	Continuous	3	Mixed models	ITT/PP
	Security scales	Continuous	3	Mixed models	ITT/PP
	FIT	Categorical	1	Independent samples T-test	ITT/PP

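### Table 4 models the parent-completed ACE-Q as a repeated safety outcome, although it appears to record a history that treatment cannot change

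*Protocol article*

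**What the plan says.** The subsection on emotional security and physical safety stands under the heading "Primary outcomes"; the secondary outcomes begin after it. It opens with the purpose of a composite instrument: "To assess the severity and intensity of the violence that children have been exposed to, a combined measure will be used". The components are the Conflict Tactics Scale (CTS), its parent-child version (CTS-pc), the Parents Report of Traumatic Impact (PRTI) and "the Adverse Childhood Experience Questionnaire (10 items, 5-point rating scale").

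The text then describes the content. The CTS-pc and PRTI items are "about problems between parent and child, and traumatic events the child has experienced". The next sentence reads: "The questionnaire also includes items about traumatic experiences in parents’ own childhood".

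Table 3 (Outcomes {12}) has the row "ACE-Q 10 p Questionnaire", where p denotes the parent, and marks it at T0, T12/14 and T13. Table 4 (Statistical methods {20a}) has the row "ACE-Q Continuous 3 Mixed models ITT/PP" in the structural emotional and physical safety block; ITT in that column means intention-to-treat, not the treatment arm. Section {20a} gives the purpose of these models: "to determine whether changes on continuous measures are different per treatment, we use linear mixed models". Its closing part names Benjamini-Hochberg for multiple comparisons and does not list the tests it covers.

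**The concern.** An outcome in a treatment comparison must be able to respond to treatment. What happened in a parent's own childhood was settled before the family entered the trial. If the ACE-Q records that, the true arm-by-time effect on the quantity measured is zero, and the model can detect only changes in how parents recall or report it.

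Those changes need not be equal across arms. In FITT, parent therapy takes up traumas within the family and the idea that each member has their own memories of a joint family story. ITT has no parent component. Nobody is blinded during the intervention. FITT parents could therefore report their childhood differently after treatment for reasons unrelated to present safety, and Table 4 would present the result in the safety block. The row also adds a test to whatever multiplicity family is used.

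**Working it through.** **1. Is the repeated administration real, or a table-layout artefact?** Summing the parent-completed items in Table 3 (CRIES, SDQ, CDC, NOSI-K, trauma-informed, IES-r, YAS-R, DPAS, CTS, CTS-pc, PRTI, ACE-Q, new incidents, SIM-PR, Security scales, in that order):

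13 + 25 + 20 + 25 + 6 + 22 + 29 + 9 + 77 + 27 + 21 + 10 + 8 + 28 + 15 = 335.

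This is the printed parent total at T0, T12/14 and T13. It assigns the 27-item part of the CTS-pc to parents and the 39-item part to children. The child total then reconciles too: 13 + 54 + 25 + 28 + 39 + 8 + 43 + 7 + 15 = 232. The 10 ACE-Q items are needed to reach 335, so the repeat is intended.

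**2. What does the ACE-Q record?** Four components are listed. The CTS, with its partner-directed example item, covers violence between partners. The CTS-pc and PRTI are tied to parent-child problems and the child's traumatic events. That leaves the ACE-Q for the parents'-childhood items. It is answered by the parent and is named for childhood experiences. This is an inference by elimination, not a statement in the protocol.

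**3. Is it set apart anywhere as a baseline variable?** No. The covariates named in {20a} are child functioning, parental psychopathology, duration, severity and intensity of violence, and new incidents. The ACE-Q appears by name only as a component, a scheduled measure and an outcome row.

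**4. The plan's own sample size.** Inputs from Sample size {14}: f = 0.18, two groups, m = 2 measurements, correlation ρ = 0.5, ε = 1, two-sided α = 0.05. For the group-by-time interaction:

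λ = f² · N · m / (1 − ρ) = 0.0324 × 64 × 2 / 0.5 = 8.294, with 1 and N − 2 = 62 degrees of freedom.

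Power is 0.809 at N = 64 and 0.796 at N = 62, so 64 reproduces. Then 3 × 32 = 96 and 96 / 0.8 = 120, as stated. The ACE-Q row enters none of these figures.

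**5. Multiplicity cost.** The Benjamini-Hochberg family is not defined. Assume that it is the primary-domain rows of Table 4: 3 for child PTSD and 10 for safety, 13 in all, or 12 without the ACE-Q. For a single true effect of the planned size, tested at the strictest threshold with N = 64:

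| Family | Strictest threshold | Power |
|---|---|---|
| 13 rows | 0.05/13 = 0.0038 | 0.457 |
| 12 rows | 0.05/12 = 0.0042 | 0.468 |

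The difference is 0.011, about one percentage point.

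**The case against.** The strongest objection concerns the inference in step 2. The sentence about parents' childhood has the combined questionnaire as its subject, and the stated purpose of that questionnaire is the violence that children were exposed to. The source cited for the ACE-Q would settle the content and is not available here. If the items concern the child, new events during follow-up could raise the score at different rates in different arms, and the true effect would not be zero by construction. This stands as a limit on certainty. It does not rescue the outcome: a lifetime history still could not fall with treatment, and new incidents already have their own 8-item measure with its own row in Table 4.

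A reader might infer that the row carries a 5% or larger chance of a false safety finding. The documents do not support that figure. It is an uncorrected rate, whereas the plan applies Benjamini-Hochberg; in the 13-row family assumed above, the strictest threshold is 0.0038. A reader might also infer a material loss of power for the real outcomes. That loss is about one percentage point, and the family behind it is itself assumed.

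It is also fair to say that nine other rows in the safety block carry most of the conclusion on safety, and that the ACE-Q row biases none of their estimates. The problem is confined to one row.

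**Conclusion.** The point holds as a matter of construct validity. Table 4 commits the protocol to testing treatment differences in change on a measure that, on the best reading of the text, describes a past fixed before randomization. Any arm-by-time difference on it would be uninterpretable as a change in safety, and unequal re-reporting is plausible in the primary FITT versus ITT contrast. The documents make such reporting change plausible; they do not show that it will occur or how large it would be.

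The conclusion rests on one disclosed inference, that the ACE-Q supplies the parents'-childhood items. On the alternative reading the score could rise but not fall, which still makes it a poor and redundant outcome. The statistical cost to the other outcomes is small, and 64, 96 and 120 are unaffected. The correction should be made because it is cheap and removes a result that could not be interpreted; the trial is not at risk from it.

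**What to change.** Before analysis, remove the ACE-Q from the outcome rows of Table 4 and from the set of tests under the Benjamini-Hochberg correction. Use its T0 score only as a baseline descriptor or covariate. Add one sentence to the outcomes section saying whose childhood the ACE-Q items concern, which would settle the inference made here.

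The cost is one table row and one sentence. Dropping the T12/14 and T13 administrations would save parents 10 of 335 items at each of those waves, but it is optional: recruitment started in March 2021, Table 3 and its totals would change, and a change judged substantial would go to the ethics committee first. If the repeats are kept, the later scores should not be reported as safety outcomes.

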#### Secondary outcomes

##### Child functioning

The Strengths and Difficulties Questionnaire (SDQ) [78] is a 25-item questionnaire using a 3-point scale (0 = not true, 2 = very true). The SDQ contains five subscales and one total scale. Subscales are (a) conduct problems (5 items), (b) emotional functioning (5 items), (c) hyperactivity/inattention (5 items), (d) peer problems (5 items), and (e) prosocial behaviour (5 items). There is a self-report and parent version. An example item is *I worry a lot*. The internal consistency of the teacher version is good. The parent and self-report versions have an internal consistency that is generally acceptable in Dutch samples [79]. In a Dutch sample, Cronbach’s alphas were between 0.76 and 0.79 for internalizing problems and between 0.82 and 0.85 for externalizing problems [80].

The Children’s Depression Inventory 2 (CDI2) [81] is a 28-item self-rated questionnaire that measures the symptoms of depression in children (7–18 years) with four subscales: negative mood/physical symptoms (9 items), negative self-esteem (6 items), interpersonal problems (5 items), and ineffectiveness (8 items). Per item, the child is asked to choose one of three sentences that best fits his/her feelings and thoughts in the past two weeks (e.g. *I am sad all the time*). The answers are calculated in a total score (ranging from 0 to 54). The internal consistency in a Dutch sample was high (*a* = 0.79), just as the test-retest reliability (*r* = 0.79) [79]. The CDI has high criterion validity and scores on the CDI correlate high with scores on other measures for depression [79].

The Child Dissociation Checklist (CDC) [82] is a 20-item parent-rated questionnaire with a 3-point Likert scale (0 = not true, 2 = very true). The child dissociation checklist is a screening instrument for dissociative problems in children (5–18 years). An example item is *Child does not remember or denies traumatic or painful experiences that are known to have occurred*. In a sample of maltreated and non-maltreated children, Cronbach’s alpha was 0.89 [83]. Discriminant validity is high [82].

##### Parent functioning

To assess parental stress, the Nijmegen Ouderlijke Stress Index—short version (NOSI-K) [84] will be used. The NOSI-K is a short version of the Parenting Stress Index [85] and a 25-item parent-rated questionnaire. The NOSI-K measures the stress related to the parent-child relationship and uses a 6-point scale (1 = totally disagree, 6 = totally agree). An example item is *I often have the feeling I cannot handle things very well*. Cronbach’s alpha for mothers and fathers is .90 and .91, respectively [86], and the NOS-K has moderate concurrent, discriminate, and criterion validity [84, 87].

To measure caregivers’ trauma knowledge, we will use a short self-report questionnaire developed for the training “Caring for Traumatized Children” [88]. The questionnaire comprises 6 items that reflect the six primary training goals, rated at a 10-point scale (1 = not accomplished, 10 = totally accomplished). Higher scores indicate higher trauma knowledge. An example item is *You know what the impact of trauma is on the development and behaviour of your child*.

Trauma symptoms in caregivers will be assessed with the Impact of Events Scale – Revised (IES-R) [89]. The Dutch version “Schokverwerkingslijst (SVL-22)” was developed by [90]. This questionnaire consists of 22 items measuring symptoms of PTSD during the last week. The SVL-22 measures three dimensions: intrusion (9 items), avoidance (8 items), and hyper-arousal (6 items). Parents rate the items on a 5-point Likert scale ranging from “not at all” (0) to “extremely” (4). An example item is *Any reminder brought back feelings about it*. Internal consistency was high (alpha = .88) [91]. Support construct validity is found in a Dutch study [90].

The Young Adult Self-Report [92] will be used to assess the psychopathology symptoms in parents. The short version of 29 items will be used in this study with items rated on a 3-point scale (0 = not true, 2 = often true). An example item is *I am too dependent on others*. The Dutch version has good reliability and validity [93]. In a Dutch study, Cronbach’s alpha was 0.92 [23].

The Daily Psychological Availability Scale [94] will be used to assess the parental availability for the child eight adapted items of the Daily Psychological Availability Scale. Items are measured using 7-point scales (1 = totally disagree, 7 = totally agree). An example item is *When I spent time with my oldest child after work today, I was not able to focus on my child*. A higher score on this scale represents more psychological availability for the child. Cronbach’s alpha was 0.78 for both fathers and mothers [94].

#### Participant timeline {13} (Fig. 1)

**Fig. 1 Fig1:**
[figure not shown]
Consort diagram

#### Sample size {14}

Power analysis was conducted to determine whether an informative trial could be conducted given limitations imposed upon the maximum sample due to the duration of the study and size of the population of children indicated for trauma treatment, using G*power 3 [95]. Sample size calculation was made based on the assumptions of the primary objective and the first secondary objective. A priori, we decided that adding systemic intervention elements to individual trauma therapy would be justified if it would mean that on average at least one out of five children would have clinically significant benefit when given the full FITT compared to treatment without systemic elements (number needed to treat = 5; equivalent to *f* = 0.18).

For primary objective 1 (Does intensive trauma therapy with a family-based component (FITT) lead to a stronger reduction of trauma symptoms and stronger increase of structural emotional safety than intensive trauma therapy without this family-based component (ITT)?), the sample size was calculated based on between 2 groups by within effect with at least two measurements (pre, end/follow-up), setting *f* = 0.18 with a power of 80% and a significance level of 5% (two-sided). Default settings were used for the correlation among repeated measures (= 0.5) and non-sphericity correction (*ε* = 1). According to the power analysis, a total sample size of 64 children is required.

Secondary objective 1 (Does intensive trauma therapy with a family-based component (FITT) lead to faster reduction of trauma symptoms and increase of structural emotional safety than low-frequency trauma treatment with parent therapy and family sessions?) is based on two measurements (pre and intermediate/follow-up). In accordance with the first sample size calculation, we tested with setting *f* = 0.18 with a power of 80%, a significance level of 5% (two-sided) was used. Again, default settings were used for correlation among repeated measures (= 0.5) and non-sphericity correction (*ε* = 1). Based on this calculation, a total sample size of 64 children is required.

The FITT sample we use to test our first hypothesis will also be used to test the second hypothesis. Taking into account loss to follow-up and measurement unreliability (20%), we set the target sample size of the multicentre randomized controlled trial on *n* = 120. Based on the number of families treated in previous years, and based on the current intakes, the recruitment of 120 families that meet the inclusion criteria seems feasible.

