Descriptive and exploratory analyses will be carried out by standard methods. All continuous scores will be examined for normality. If variable distributions deviate too much from normality, corrective steps will be taken either by transforming variables or by using non-parametric tests. We will control for child functioning, parental psychopathology, duration, severity, and intensity of interparental violence, and new IPV incidents. The variables are treated as covariables in the analyses mentioned below.

To examine our primary hypothesis, linear mixed models will be used in case of continuous data. GEE will be used for the categorical data. We will use the end of treatment (T12/T14) and intermediate/follow-up time-point (T13) to compare FITT with ITT (objective 1).

To examine our secondary hypotheses, linear mixed models will be used. We will use the end of treatment time-point (T12/T14) to compare FITT with TAU. Control measures are child functioning; parental psychopathology; duration, severity, and intensity of interparental violence; and new IPV incidents. The variables are treated as covariables in the up-mentioned analyses. We will use the Benjamini-Hochberg method to correct for multiple comparisons.

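### The sample size section enters an f that matches NNT = 5 only as a between-group effect into a group-by-time interaction calculation, so 64 children give less than 80% power for that benefit under most readings

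*Protocol article*

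**What the plan says.** Sample size {14} of the protocol article defines the target before any calculation. The systemic elements are worth adding if "at least one out of five children would have clinically significant benefit when given the full FITT compared to treatment without systemic elements". This is then put on an effect-size scale: "number needed to treat = 5; equivalent to *f* = 0.18". The article does not show the conversion and gives no control response rate.

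For the primary FITT–ITT comparison the calculation, made in G*Power 3, is for a "between 2 groups by within effect with at least two measurements (pre, end/follow-up" measurement, with f = 0.18, 80% power and two-sided 5% significance. "Default settings were used for the correlation among repeated measures (= 0.5) and non-sphericity correction (*ε* = 1". The result: "According to the power analysis, a total sample size of 64 children is required". The next paragraph of the section reuses the same f, settings and N for secondary objective 1 (FITT against TAU). The target of 120 randomised follows after a 20% allowance; Trial design {8} gives 96 completers, that is 32 per arm.

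**The concern.** Cohen's f depends on the contrast it describes. A given difference between two groups after treatment has one f in a between-group comparison and a smaller one in a group-by-time interaction. The printed 0.18 is what NNT = 5 gives on the between-group scale, but it was used on the interaction scale.

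The section presents the power analysis as a test of whether an informative trial is possible within the available population, and it ties NNT = 5 to whether the family component is justified. If power for that benefit is well below 80%, a non-significant FITT–ITT result says much less about the component than the section implies.

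**Working it through.** **Inputs (Sample size {14}).** NNT = 5; f = 0.18; 2 groups; m = 2 measurements; ρ = 0.5; ε = 1; two-sided α = 0.05; N = 64.

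**1. The plan's own figure.** For the within-between interaction, λ = f²·N·m/(1 − ρ), with 1 and N − 2 degrees of freedom.
- N = 64: λ = 0.0324 × 64 × 2/0.5 = 8.29, power 80.9%.
- N = 62: power 79.6%.

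So 64 reproduces exactly, which also confirms the scale on which f was entered. The inflation reproduces too: 64/2 = 32 per arm, 3 × 32 = 96, and 96/0.80 = 120.

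**2. Where 0.18 comes from (inferred).** The usual conversion is NNT = 1/(2Φ(d/√2) − 1). With NNT = 5, Φ(d/√2) = 0.60, so d = √2 × Φ⁻¹(0.60) = 0.358. For two equal groups the between-group f is d/2 = 0.179, which rounds to the printed value.

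**3. The same difference as an interaction.** With equal baselines and a post-treatment difference of d SD, the four cell means are 0, 0, 0 and d. Removing the grand mean and both main effects leaves interaction effects of ±d/4. The interaction f is therefore 0.358/4 = 0.0896, about 0.09. In reverse, f = 0.18 implies d = 4 × 0.18 = 0.72, and NNT = 1/(2Φ(0.72/√2) − 1) = 2.57.

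**4. Power for d = 0.36 with 64 children, ρ = 0.5.**
- Change scores: λ = 0.0081 × 64 × 2/0.5 = 2.07, power 29% (simulation 29%).
- Baseline-adjusted: residual SD √(1 − 0.5²) = 0.866, power 37%.
- Mean of two post-treatment scores, baseline-adjusted (an assumed model): residual variance (1 + 0.5)/2 − 0.25 = 0.5, power about 51%.
- All 80 randomised children in the pair retained, single post-treatment score: 35–36% on change, 45% adjusted.

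For 80% power the two-arm comparison needs about 246–248 children on change, or 184–186 adjusted, before dropout. With 64 children, 80% power is reached at d of about 0.71 on change or 0.62 adjusted.

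**5. Cross-check.** At ρ = 0.5 a change score has variance 2(1 − 0.5) = 1, the same as a single post-treatment score. A plain two-group comparison at d = 0.36 needs 246 children, so analysing change cannot reduce that to 64. The ratio 246/64 = 3.8 is close to the square of the factor of two in f.

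**6. Responder reading.** Suppose instead that NNT = 5 means a 20-point difference in response rate. Then d = Φ⁻¹(p + 0.20) − Φ⁻¹(p), where the control rate p is an assumption because the article gives none. Power is for 32 per arm:

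| Control rate | d | Change | Adjusted |
|---|---|---|---|
| 11% or 69% | 0.73 | 82% | 91% |
| 20% or 60% | 0.59 | 64% | 76% |
| 30% or 50% | 0.52 | 54% | 66% |
| 40% | 0.51 | 51% | 63% |

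Across control rates of 20–60% the between-group f would be 0.25–0.29, so this reading does not yield the printed 0.18 either.

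**7. Sensitivity to ρ at d = 0.36 (change / adjusted).** ρ = 0.7: 45% / 51%. ρ = 0.8: 61% / 66%.

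**The case against.** Three objections carry weight.

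First, the conversion is not printed, so a between-group f being carried over is an inference. That stands. But the usual conversion returns 0.179, and on the interaction scale 0.18 corresponds to NNT = 5 only at control response rates near 11% or below, or 69% or above. The article states no such rate.

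Second, the section's words describe children who benefit, which fits a responder difference at least as well as the conversion in step 2. That also stands, and it raises the figures to 51–76% for a single post-treatment score at control rates of 20–60%.

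Third, the planned analysis may be stronger than a two-point change score. The section says at least two measurements, and Statistical methods {20a} uses both end of treatment and follow-up in mixed models. Averaging two post-treatment scores with baseline adjustment gives about 51% at d = 0.358. Combined with the responder reading at control rates of 20–60%, it gives 81–91%. So one favourable pairing of assumptions does reach 80%. It is not the calculation the article reports, and the model form is assumed.

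A reader might infer that 29% is simply the trial's power. It is the power for one conversion and a change-score analysis, near the low end of the range at ρ = 0.5. A reader might also infer a further loss from testing many primary measures. The documents do not support a figure for that: in Table 3 the CAPS-CA and the FIT are not taken at both post-treatment points, Outcomes {12} describes four of the violence scales as one combined measure, and the planned correction is Benjamini-Hochberg, so a Bonferroni threshold would not represent it.

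**Conclusion.** The point holds. N = 64 is computed correctly from f = 0.18, but the stated equivalence with NNT = 5 does not hold for the interaction test used. On the usual conversion f is too large by a factor of two, and the section's own method gives about 29% power on change for d = 0.36 (37% with baseline adjustment) instead of 80%. The responder reading gives 51–64% on change and 63–76% adjusted at assumed control rates of 20–60%. What 32 per arm do give at 80% is a difference in change of about 0.7 SD, an NNT of about 2.6.

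These figures rest on ρ = 0.5, equal baselines, equal variances and a continuous outcome. The FITT–TAU calculation for secondary objective 1 has the same fault, so both calculations behind the target of 120 are affected.

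The documents do not say that a null result will be taken as proof that the family component is not worth adding. That is a risk which the overstated power creates, not a stated plan. Nor does the finding show that the trial should be enlarged: the section says that the sample is limited by study duration and population.

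**What to change.** Keep 120 families and amend Sample size {14}:

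- Remove the statement that NNT = 5 equals f = 0.18, or restrict it to a between-group comparison.
- State that 32 completers per arm give 80% power for a difference in change of about 0.7 SD (NNT about 2.6).
- State the lower power for NNT = 5, naming the conversion used and giving its range: for example about 29–37% at d = 0.36, or 51–76% for a 20-point responder difference at assumed control rates of 20–60%.
- Make the same correction for secondary objective 1.
- Say that the statement applies to a continuous outcome analysed by mixed model. It does not cover the CAPS-CA as classified in Table 4, where it is categorical and analysed by GEE.
- Commit to reporting the FITT–ITT difference with its 95% CI against the justifying effect, so that a non-significant result is not read as showing no worthwhile benefit.

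The cost is a revised paragraph and one reporting commitment. No more families are needed and no analysis changes, but the stated power becomes less favourable.
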